#### Regression Analysis for Variables Prediction

A generalized linear modal (GLM) will be used for regression analysis of co-variation (e.g., emotion and mood state) and of the follow-up long-term effects by SPSS 21.0. The selected model with different statistics will be specified based on data characteristics such as the type of distribution. For example, a multiple linear regression model will be introduced according to stepwise regression to test whether there was any potential influencing factor among secondary indicators.

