### Outcome Measures

#### Primary Outcome Measure

We will evaluate the short-term effects of Retrieval-TBS treatment in the reduction of cue-induced drug craving and cue reactivity by comparing EEG in VR scene between baseline (T0) and post-test (T3).

***EEG*** will be recorded by a portable EEG system (Muse by Interaxon Inc.) during each VR session (3 min/scene × 1 MA-related VR scene and 1 neutral-related VR scene = 6 min) at T0 and T3, respectively. Each patient will wear an EEG headset before entering the VR scenes. Four channels (refer to EEG 10-20 system: FP1, FP2, TP9, TP10) and an original reference (FPz) will be retained to measure the brainwave spectrum including delta, theta, alpha, beta and gamma (with a sample rate of 256 Hz and 12 bit resolution), frequency bands between 45 and 60 Hz were omitted because muse hardware applied notch filters at 50 and 60 Hz to reduce environmental noise (67). According to a previous study, there was a significant difference between drug-cue and neutral-cue-induced EEG activities (68). In terms of drug-cue related memory, the frontal theta activity used as a feedback signal in adaptive regulation was highlighted for memory updating (69), which has been suggested as an indicator of the enhanced binding of incoming interconnected information in memory formation (70), while the beta activity which reflects a memory promoting state (70) indicated the level of memory integration in reconsolidation (71). Since the wearable devices available in VR have been applied to classify emotional states (72), we plan to use wearable EEG combined with VR scenes to observe the brain activity associated with memory in the current study. The average power in EEG frequency bands (i.e., δ = 1–4 Hz, θ = 4–8 Hz, α = 8–13 Hz, β = 13–30 Hz, γ = 30–50 Hz) are real-time computed in hardware and sent alongside an indicator of data quality from each sensor. The Muse manufacturer provided on-device computed FFTs (https://sites.google.com/a/interaxon.ca/muse-developer-site/museio) were used to estimate the spectral power density (μV2/Hz) for frontal electrodes in each frequency band in this study. EEG spontaneous measures at the frontal sites were calculated, as shown in Figure 2, by 1 min post-dark data minus 1 min pre-dark data in each frequency band in each VR scene. We used state-related EEG to calculate the EEG activities for drug-related craving state in VR, because cue-induced craving is related to a tonic, slowly changing craving state and Muse is a portable device that may not stably acquire EEG activities during walking in VR scene. Previous studies have used “state-related EEG” to compare different EEG activities in different state (56, 72, 73). Because of the non-normal distribution, power density value and ratios were log-normalized. For statistical tests, a two-tailed alpha of 0.05 was used unless explicitly stated otherwise.

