### Sample Size

According to Hanlon et al. (28) study, 25 cocaine users either receiving active- or sham- pre/post TBS treatment showed a significant difference in the reduction of cue craving (*F*_1, 96_ = 5.65, *P* = 0.02). The effect size (*f*= 0.2496) calculated by formula $r^{2}=\frac{df1^{*}F}{df1^{*}F\;+\;df2},f=\sqrt{\frac{r^{2}}{{1-r}^{2}}}$, the 3 (between factor: MA VR-active TBS vs. MA VR-sham TBS vs. neutral VR-active TBS) × 4 (within factor: four repetitive tests) design of the current protocol, the proposed alpha error (α = 0.05) and power (β = 0.95) will be used as the parameters for a prior sample size calculation (in G.Power 3.1). The required sample size is 45 in terms of repeated measures ANOVA with within × between interaction effect.

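### Stepwise regression cannot validly test for influencing factors: with no true factor, it would still report one in roughly 11 to 26% of analyses with three to six candidates

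*Protocol article*

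**What the plan says.** The section Regression Analysis for Variables Prediction assigns a generalized linear model to covariates such as emotion and mood, and to the long-term follow-up effects. The model is to be settled from the data: "The selected model with different statistics will be specified based on data characteristics such as the type of distribution". The one concrete procedure, offered as an example, is that "a multiple linear regression model will be introduced according to stepwise regression to test whether there was any potential influencing factor among secondary indicators".

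The section sets no error level of its own. The general rule, under Primary Outcome Measure, is that "a two-tailed alpha of 0.05 was used unless explicitly stated otherwise". The Sample Size section ties the number of participants to a different analysis: "The required sample size is 45 in terms of repeated measures ANOVA with within × between interaction effect".

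The Abstract and the Secondary Outcome Measures section name the measures that could serve as candidates: VAS craving, cue-induced heart rate, SAS, SDS and POMS-SF, with substance-taking history as a further possible covariate.

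**The concern.** Stepwise selection takes the candidate with the smallest p-value and then prints that p-value as if the candidate had been chosen in advance. The printed p-value is too small, the interval is too narrow and centred too far from zero, and R-squared is too high. Used to describe data, this is a weakness. Here the article gives the procedure the task of testing whether a factor exists, which it cannot do at the stated 0.05.

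At stake is a false report that, say, baseline anxiety or mood influences the response, supported by a significant coefficient and a respectable share of explained variance.

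**Working it through.** **Inputs from the article.** N = 45 (15 per arm); alpha 0.05, two-tailed; candidates drawn from the measures named above. Counting each as one score gives three candidates if only the emotion and mood questionnaires are entered, five with VAS and heart rate, and six with substance-taking history.

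**Assumptions, because the article does not give them.** Number of candidates: 3, 5 or 6. Common correlation between candidates: 0 to 0.7. Entry at p < 0.05, removal at p > 0.10. One dependent variable.

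**Step 1: the plan's own figure.** The article gives no error rate for the regression, so the only figure to reproduce is N = 45. For a within–between interaction with k = 3 groups and m = 4 measurements, λ = f²·N·m/(1 − ρ). With the stated f = 0.2496 and an assumed ρ = 0.5 and no sphericity correction, λ = 0.0623 × 45 × 4 / 0.5 = 22.4. The degrees of freedom are (3 − 1)(4 − 1) = 6 and (45 − 3)(4 − 1) = 126, and power is 0.955. N = 45 therefore reproduces from the stated f. It sizes the ANOVA interaction and has no bearing on the regression.

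**Step 2: closed-form check.** With k independent candidates, each screened at 0.05, the chance of at least one false entry is 1 − 0.95^k:
- k = 3: 14.3%
- k = 5: 22.6%
- k = 6: 26.5%

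**Step 3: simulation.** Stepwise selection with N = 45, an outcome unrelated to every candidate, and 1,500 runs per setting. The entries are the share of runs that select at least one factor, with the mean R-squared of the selected model in brackets.

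| Candidates | correlation 0 | 0.3 | 0.5 | 0.7 |
|---|---|---|---|---|
| 3 | 12.9% (0.119) | 12.9% (0.130) | 12.9% (0.131) | 10.9% (0.127) |
| 5 | 21.9% (0.137) | 21.4% (0.135) | 19.5% (0.136) | 16.1% (0.142) |
| 6 | 25.7% (0.138) | 24.9% (0.146) | 19.7% (0.145) | 17.9% (0.153) |

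The simulation error near 16% is √(0.16 × 0.84 / 1500) ≈ 1 percentage point. A separate simulation put the low end for five to six candidates at 15%, so I give that range as 15–26%.

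**Step 4: is the sample size the cause?** With six independent candidates and n = 450, a false factor is selected in 29.1% of runs (1,000 runs), against 25.7% at n = 45. The rate does not fall as n grows. The apparent effect does: mean R-squared is 0.014 at n = 450 and 0.138 at n = 45. The entry rule explains this. A single factor enters only if |t| exceeds its critical value, and R² = t²/(t² + n − 2):
- n = 45: t = 2.017, so R² is at least 4.07/(4.07 + 43) = 0.086
- n = 450: t = 1.965, so R² is at least 3.86/(3.86 + 448) = 0.009

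**Step 5: is the stepwise algorithm alone the cause?** A fixed model containing all candidates, with no selection, was read coefficient by coefficient at 0.05 under the same null. At least one coefficient is significant in about 21–22% of runs with five covariates and about 25% with six. That is close to the stepwise rate. A single overall F test of the covariate set rejects in about 5%.

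**The case against.** The strongest reply has four parts.

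*The rate measures multiplicity rather than stepwise selection.* Step 5 bears this out. Dropping stepwise but still reading every coefficient at 0.05 would leave the rate almost unchanged, so the remedy must include an overall test or an adjustment. What belongs to stepwise selection itself is that the printed p-values, intervals and R-squared are conditional on a search they ignore.

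*The rate compares a family-wise figure with a per-test alpha, and the article never promises family-wise control here.* That is correct as a description. But the stated question is whether any factor exists, and for that question the chance of any false factor is the relevant error.

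*The inputs are unknown, and a fuller plan may hold the candidate list and limits.* This stands as far as the exact size goes, and I do not count their absence against the article. It does not remove the point, because the article itself names the method and its purpose. With only three candidates the rate is about twice 5%, not several times.

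*The analysis is secondary and given as an example.* This also stands. Treatment effects are assigned elsewhere, to the paired t-test, the ANOVA or their non-parametric counterparts.

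A reader might infer three stronger claims that the article does not support. One is that 45 participants cause the false findings; step 4 shows otherwise. Another is that the primary result is compromised; it does not pass through this regression. The third is that the rate reaches about 40%. That needs around eleven candidates, for which simulation gives 24–43%, and such a count would require something like POMS-SF subscales, which the article does not describe.

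**Conclusion.** The point holds in a limited form. The article fixes a method that cannot do the testing it is given. If nothing matters, the search reports at least one factor in roughly 11–13% of analyses with three candidates and 15–26% with five or six, against a nominal 5%. The selected model then shows an R-squared of about 0.12–0.15 at N = 45.

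These figures rest on the assumed candidate count, correlation and entry and removal limits, and on a single dependent variable. Repeating the search over several outcomes, such as the five EEG bands, would raise them. The change is worth making before the data are analysed, but it concerns a secondary analysis only.

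**What to change.** Replace the stepwise sentence with one pre-specified linear model containing treatment arm, the T0 value of the outcome and a short fixed list of T0 covariates, named before the data are seen. Then:

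- Judge the covariates as a set by one overall F test at 0.05, given arm and the T0 outcome. Alternatively, adjust the individual coefficients for multiplicity, for example by Holm.
- Report every coefficient with its 95% interval, significant or not. If Holm is used, say that the intervals are unadjusted.
- Label the analysis exploratory.

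With three single-score covariates, the model leaves 45 − 1 − 2 − 1 − 3 = 38 residual degrees of freedom, which is workable. The list should stay about that short.

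The cost is a sentence or two of analysis text and a decision on the covariates. No data, visits or participants are added. The sponsor will have fewer significant predictors to report, and a real factor left off the list will not be found by this analysis.

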### Monitoring

#### Definition of Adverse Events and Potential Risks

(1) referring to previous neuro-modulation studies, rare cases reported adverse effects of TMS, although some tolerable but uncomfortable feelings were reported by participants, such as mild itching, numbness or tingling, a slight headache, or head discomfort. However, these symptoms only existed for a short time and were relieved after stimulation ceased;

(2) according to existing cases and clinical practices, patients with following conditions are at higher risk to experience adverse sides in the treatment: (1) experiencing epileptic seizures or whose immediate family member has a history of epilepsy and mental illness; (2) having a history of brain diseases such as brain trauma, cerebral hemorrhage, cerebral infarction, or intracranial infection; (3) having intracranial metal or other foreign bodies;(4) having a pacemaker placed in the body.

#### Identification Method and Management System

(1) above potential risks will be considered within exclusion criteria to select adequate participants at the screening stage. These criteria will be re-confirmed again before the delivery of stimulation;

(2) individualized parameters for treatment: the intensity will be identified as RMT according to the individual threshold, and it will be adjusted (80–110% RMT) based on the tolerance of each patient;

(3) if there is persistent pain, intolerable, or the participant subjectively requests to withdraw, the treatment shall not be continued and concomitant care will be offered.

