##### TBS Pattern

The cTBS will be applied to reduce activation of the OFC circuit. TBS sessions will be carried out with a hand-held figure-of-eight coil with the size of 90 mm diameter of one half of the “8” shape (B9076, Yiruide Co., Wuhan, China), attached to a YRD CCY-I stimulator (Yiruide Co., Wuhan, China). Following a 10-min rest after memory retrieval, participants either in the MA VR scene + TBS group (*n* = 15) or in the MA VR scene + sham TBS group (*n* = 15) or in the neutral VR scene + TBS group (*n* = 15) will receive two TBS sessions within 1 week. In each session, all participants will receive two 1,800-pulse trains of cTBS in 5 min (three pulses are given at 50 Hz as one burst; a burst will be given every 200 s as 5 Hz; one train for 120s, containing 1,800 pulses) with a pulse intensity of 80% of RMT following Hanlon et al. (62)'s suggestion. A 60-s break will give to participants after the first train (1,800 pulses). The choice of TBS intensity will consider the participants' real-time feedback and health condition to TMS stimuli. If a participant reported unbearable discomfort with TBS stimulation, we will turn down the intensity gradually until acceptable. If a participant still reported unbearable discomfort when the stimulation intensity was lower than 60% of the RMT, this participant will withdraw from the experiment. These parameters have been applied by previous studies (62) and proposed in safety guidelines (63).

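### The two sections that set stimulation intensity contradict each other: 80% of RMT with reductions only, against adjustment within 80–110% of RMT

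*Protocol article*

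**What the plan says.** The TBS Pattern section describes two trains per session, delivered "with a pulse intensity of 80% of RMT". It adds in general terms that the choice of intensity takes account of the participant's feedback and health. The only adjustment it then describes is a reduction: for unbearable discomfort, "we will turn down the intensity gradually until acceptable". If unbearable discomfort is still reported "when the stimulation intensity was lower than 60% of the RMT, this participant will withdraw from the experiment". The section closes by saying that its parameters have been used in earlier work and appear in safety guidelines.

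The Identification Method and Management System section, under Monitoring, states that "the intensity will be identified as RMT according to the individual threshold", and continues: "it will be adjusted (80–110% RMT) based on the tolerance of each patient". Its next item stops treatment for persistent pain, intolerance or a request to withdraw.

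Two other sections mention intensity. The Intervention section says only that it is assigned from the individual RMT. The Intensity Identification section explains how RMT is measured but gives no treatment intensity. Neither settles the matter.

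On burst timing, the TBS Pattern section says "three pulses are given at 50 Hz as one burst" and "a burst will be given every 200 s as 5 Hz", with a train of 120 s and 1,800 pulses.

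**The concern.** Intensity is part of the definition of the experimental treatment. Two sections govern it, both tie adjustment to tolerance, and they give different ranges and different directions. An operator following one section would depart from the other as soon as the intensity moved away from 80% of RMT.

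Three things are at stake.

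- **Treatment content.** Groups A and C both receive active stimulation, and the comparison between them is meant to isolate the retrieval scene. Under Study Design, the doctors who deliver stimulation know the allocation. Two available intensity rules leave these unblinded operators a choice that need not be made alike in A and C.
- **Retention.** A participant who cannot tolerate 80% may continue at a lower intensity under one section and has only stopping under the other. With 15 participants per group, each such case is 1/15 = 6.7% of a group.
- **Justification.** The statement about earlier use and safety guidelines stands in the TBS Pattern section and refers to the parameters given there. The article does not show that it extends to intensities above 80% of RMT.

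**Working it through.** **Intensity, the two rules side by side**

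| | TBS Pattern | Identification Method and Management System |
|---|---|---|
| Stated intensity | 80% of RMT | identified as RMT, then adjusted |
| Reason for adjustment | unbearable discomfort | tolerance |
| Direction described | down only | anywhere within 80–110% |
| Range described | 80% down to about 60% | 80% to 110% |
| If not tolerated | withdrawal if discomfort persists below 60% | treatment stopped; no step below 80% |

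The first range runs from about 60% to 80%, the second from 80% to 110%, so their overlap is the single value 80%. Every increase above 80% has support only in the Monitoring text. Every reduction below 80% has support only in TBS Pattern.

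The size of the disagreement, taken separately for the two kinds of participant to whom the rules apply:

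- Tolerates stimulation well: 80% under one section, up to 110% under the other. Ratio 110/80 = 1.375.
- Cannot tolerate 80%: reduced towards 60% under one section, not below 80% under the other. Ratio 80/60 = 1.33. Because 60% triggers withdrawal only if discomfort persists, it is not an absolute floor, and this ratio is approximate.

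Read literally, the phrase that intensity is identified as RMT would make 100% of RMT the starting point. It may mean only that the threshold is measured individually, so nothing here rests on it.

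**Burst timing**

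Inputs, all from TBS Pattern: 3 pulses per burst, 5 Hz, 120-s trains, 1,800 pulses per train, two trains, a 60-s break, a 5-min session.

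- Pulses per train = duration × burst frequency × pulses per burst = 120 × 5 × 3 = 1,800. This reproduces the stated count.
- Session length = 120 + 60 + 120 = 300 s = 5 min. This reproduces the stated length.
- With one burst every 200 s: frequency = 1/200 = 0.005 Hz, and 120 × 0.005 × 3 = 1.8 pulses. This does not reproduce the count, and a 200-s interval does not fit within a 120-s train.
- A frequency of 5 Hz corresponds to an interval of 1/5 = 0.2 s, that is 200 ms.

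The frequency, train duration, pulse count and session length agree with one another; only the printed interval disagrees, in a way that fits seconds written for milliseconds.

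**The case against.** **Size.** A reader might pool the two sections into a span of 60% to 110% and infer that two compliant operators could differ 110/60 = 1.83-fold. The documents do not support that for any one participant. An intensity near 60% is reached only by someone reporting unbearable discomfort, and the Monitoring rule, which also depends on tolerance, would not take that person to 110%. The ratios of about 1.33 and up to 1.375 are the fair ones.

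**Safety.** A reader might also infer that part of the 80–110% range is unsafe, or that the safety statement in TBS Pattern cannot cover it. Nothing in the article shows either, and the cited sources are not available here. The article also has safeguards: exclusion of candidates whose threshold exceeds 50% of the stimulator's maximum output, a short trial of stimulation before the full session, exit for intolerable reactions, and stopping for persistent pain. What remains is that the statement is not shown to extend above 80% of RMT.

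**Direction.** TBS Pattern does not expressly forbid an increase, and its sentence on feedback and health is general. That is so, but a reduction is the only adjustment it describes. This reading also leaves the lower end unresolved, because reductions below 80% remain outside the Monitoring range.

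**Heterogeneity.** Adjustment for tolerance varies the delivered intensity even under TBS Pattern alone, so only the additional spread above 80% comes from the contradiction. No effect on the sample size or the analysis method has been shown.

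**Burst interval.** The 1,000-fold gap between 200 s and 0.2 s (200/0.2) looks alarming, but the interval could not be delivered as printed and the surrounding figures reveal the slip. It is clerical.

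**Condensed article.** A full protocol might say more. That would excuse an omission, but these are two incompatible statements in the same text. It does excuse the article for not saying how delivered intensity is recorded, and no finding is made on that.

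**Conclusion.** The intensity rules are wrong as written. They coincide only at 80% of RMT, differ by a factor of up to 1.375 for a participant who tolerates stimulation well, and differ by about 1.33, or between stepping down and stopping, for one who does not. The consequence is that the content of active treatment in groups A and C, and retention, depend on which section an unblinded operator follows.

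This rests on two readings: that both sections govern the same treatment stimulation, and that TBS Pattern provides for reductions only. How many participants would be affected cannot be derived from the article. The conclusion does not extend to a two-fold dose difference, to a demonstrated hazard, or to any fault in the sample size or analysis. The burst interval is a separate, minor editorial error.

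**What to change.** The sponsor and clinical team should reconcile the TBS Pattern section with the Identification Method and Management System section, so that the protocol contains one intensity rule with one permitted range, one stated direction of adjustment, and one consequence for a participant who cannot tolerate the stimulation. Which rule is right is a clinical decision on which this review takes no position. The statement on earlier use and safety guidelines should then be checked against whatever range is kept.

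In the same correction, the burst interval should be brought into agreement with the stated frequency, train duration and pulse count.

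The cost is a text correction and notification of the ethics committee. The sample size and the analysis do not change.
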